#### Secondary outcome

Proportion of patients classified by the decision support tool as low-risk in relation to sex and age.The proportion of patients, among those classified by the decision support tool as low-risk in relation to sex and age, who at follow-up turn out to have a high-risk condition.Proportion of patients among those who have been classified as low-risk and transported to an ED and who have been admitted to a ward (discrepancy between the assessment by the decision support tool and the assessment in the ED).Distribution of final diagnoses in the above-mentioned group.In retrospect, the predictive ability of the decision support tool regarding both low-risk and high-risk patients.

### Definitions

Risk condition classification is based on the diagnosis given at discharge from the hospital according to the physician in charge. A low-risk condition is defined as a diagnosis with no medical need for hospital treatment, suitable for non-conveyance. This also includes patients with chest pain who remain on scene, who do not visit the ED within 72 h and who do not die within 7 days.

A high-risk condition is defined as a time-sensitive condition with relatively high mortality rate in need of immediate medical care when seen retrospectively, for which transport to the hospital with highest priority is called upon. These definitions are the same as those used in BRIAN 1 [6].

An intermediate-risk condition is defined as a diagnosis probably in need of hospital care but for which time is not judged to be a critical factor. That is, it does not fulfil either of the definitions above.

### Statistical analyses

Descriptive data will be presented as mean and standard deviation or median and interquartile range for numeric variables, while numbers and percentages will be reported for categorical variables. Univariable analysis will be conducted using logistic regression, adjusted for age, and odds ratios with 95% confidence intervals will be presented.

A multivariable prediction model for acute chest pain will be developed using multivariable logistic regression with stepwise selection, LASSO logistic regression, two-stage LASSO, and adaptive LASSO. Additionally, machine learning models using classification trees, gradient boosting trees, and/or random forests will be applied. Hyperparameter tuning for the LASSO and machine learning methods will be conducted to minimise the model’s using cross-validation deviance. Model performance will be evaluated using pseudo-R-square for overall performance, along with receiver operating characteristic (ROC) curves and area under the curve (AUC) for discriminatory assessment. Bootstrapping will be used for internal validation. Calibration will be assessed using calibration-in-the-large, calibration slope, and calibration plots. Variable importance of the included predictors will be evaluated by multivariable R-square decomposition using Shapley values. Missing data will be handled using multivariate imputation by chained equations to capture complex nonlinear relationships and interactions in the data.

Subgroup analyses will focus on the additional clinical utility of prehospital Troponin I in high-risk patients not identified as such by the current EMS triage system/guidelines — specifically, patients transported to the emergency department (ED) without obvious signs of a time-sensitive condition. Additionally, analyses will be considered by age and sex to determine in where the model demonstrates the highest clinical utility.

All statistical tests will be conducted at the 5% significance level. Statistical analyses will be conducted using the R language and environment for statistical computing (R Core Team, Vienna, Austria) and the Python programming language (Python Software Foundation, Delaware, United States).

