**Methods and analysis:**

This is a prospective, multicentre, cohort study including adult unselected EMS patients with chest pain. Data is being collected from 20 May 2023 to 31 December 2025, aiming to include at least 2,000 patients. High-sensitivity troponin I is being analysed bedside using Siemens Healthineers Atellica VTLi. In addition to prehospital troponin I, data is being collected on patient medical history, onset, vital signs, symptoms, ECG and diagnosis at hospital discharge. Several statistical analyses (random forest, logistic regression, gradient boosting) will be conducted to identify the best model for identifying patients with low-risk conditions suitable for non-conveyance.

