### Outcome measures

#### Primary outcome

Proportion of patients classified as low-risk by the decision support tool.The proportion of patients, among those classified by the decision support tool as low-risk, who at follow-up turn out to have a high-risk condition.

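### One bootstrap rule with no named variant covers regression and tree ensembles alike; run as the usual optimism correction, it would leave tree-model performance overstated

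*Protocol article*

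**What the plan says.** All of this is in the protocol article.

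- **Models (Statistical analyses).** The regression family is "multivariable logistic regression with stepwise selection, LASSO logistic regression, two-stage LASSO, and adaptive LASSO". In addition, "machine learning models using classification trees, gradient boosting trees, and/or random forests will be applied".
- **Tuning (same section).** "Hyperparameter tuning for the LASSO and machine learning methods will be conducted", with cross-validated deviance as the criterion. This is the only use of cross-validation that the section mentions.
- **Performance (same section).** "Model performance will be evaluated using pseudo-R-square for overall performance", together with ROC curves, AUC and calibration measures.
- **Validation (same section).** "Bootstrapping will be used for internal validation". No variant is named, and model families are not distinguished.
- **Purpose (Abstract, Methods and analysis).** "Several statistical analyses (random forest, logistic regression, gradient boosting) will be conducted to identify the best model". The measure that decides which model is best is not given.
- **Safety outcome (Primary outcome).** "The proportion of patients, among those classified by the decision support tool as low-risk, who at follow-up turn out to have a high-risk condition".

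**The concern.** In the optimism-corrected bootstrap, each model is refitted on a resample and scored twice: on that resample and on the original patients. The mean difference is taken as the optimism and subtracted from the apparent performance. The original patients are not independent of the resample, because most of them are in it. A regression with a limited number of coefficients cannot reproduce individual patients, so the overlap matters little. A deep forest or a flexible boosted model can largely memorise its training patients. It scores well on both sets, the difference is small, and too little is subtracted.

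Two things are at stake. The study compares model families, and a correction that works for one family and fails for another does not compare them fairly. And the share of missed high-risk patients is a primary outcome that bears on whether the tool is ready for routine use (Scientific questions). The error would run in the unsafe direction.

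**Working it through.** **1. The plan's own figure.** The Sample size section assumes an event rate of 0.68, an AUC of 0.85 and 80 parameters, and reports 1,857 patients. A binormal approximation gives a Cox-Snell R² of 0.315, with a maximum of 0.715.

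- Criterion (i): n = P / [(S − 1) ln(1 − R²/S)] = 80 / [(−0.1) × ln(1 − 0.315/0.9)] = 1,857.
- Criterion (ii): S = 0.315/(0.315 + 0.05 × 0.715) = 0.898, so n ≈ 1,817.
- Criterion (iii): (1.96/0.05)² × 0.68 × 0.32 = 334.4, so 335.

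The stated figure reproduces and is not in question. It supplies the setting for the simulations.

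**2. Overlap.** The chance that a given patient is in a resample of 2,000 is 1 − (1 − 1/2000)^2000 = 0.632.

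**3. Simulated AUC.** From the documents: n = 2,000, an event rate of 68%, and about 15% high-risk (Introduction). Assumed: predictor distributions, the form of the true model and the tuning grids. Settings A to D used 3 data sets, 10 to 12 resamples each, and 20,000 to 30,000 new patients for the true value. The last column is corrected minus true.

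| Setting | Model | Optimism-corrected | Out-of-bag | True | Overstatement |
|---|---|---|---|---|---|
| A: 68%, 66 predictors, additive truth | Forest, leaf 1 | 0.974 | 0.815 | 0.830 | 0.144 |
| | Forest, leaf 10 | 0.922 | 0.827 | 0.841 | 0.081 |
| | Boosting | 0.876 | 0.829 | 0.845 | 0.031 |
| | LASSO | 0.858 | 0.852 | 0.868 | −0.010 |
| B: 68%, 80 predictors, linear truth | Forest, tuned | 0.965 | 0.799 | 0.812 | 0.153 |
| | Boosting, tuned | 0.888 | 0.813 | 0.825 | 0.063 |
| | Logistic | 0.863 | 0.849 | 0.856 | 0.007 |
| C: as B, 15% high-risk | Forest, tuned | 0.961 | 0.796 | 0.798 | 0.163 |
| | Boosting, tuned | 0.900 | 0.813 | 0.811 | 0.089 |
| | Logistic | 0.867 | 0.849 | 0.847 | 0.020 |
| D: 68%, 60 predictors, thresholds and interactions | Forest, leaf 1 | 0.969 | 0.771 | 0.781 | 0.188 |
| | Forest, leaf 10 | 0.931 | 0.779 | 0.792 | 0.139 |
| | Boosting | 0.878 | 0.800 | 0.803 | 0.075 |
| | Logistic | 0.679 | 0.659 | 0.671 | 0.008 |
| E: about 12% events, additive truth | Deep forest | 0.94 | – | 0.65 | 0.29 |
| | Forest, leaf 30 | 0.84 | – | 0.70 | 0.14 |
| | Boosting | 0.77 | – | 0.70 | 0.07 |
| | Logistic | 0.72 | – | 0.73 | −0.01 |

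In every setting the optimism correction puts a forest first, and in none is a forest truly best. Tuning by cross-validated deviance (B and C) did not prevent this. In A to D the out-of-bag estimates lie within 0.02 of the truth and give the true order.

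**4. The safety outcome.** Setting C, with the 40% of patients at lowest predicted risk called low-risk (an assumed cut). High-risk share, corrected / out-of-bag / true:

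- Forest, tuned: 0.4% / 3.8% / 3.6%, a 9-fold understatement (3.6/0.4).
- Boosting, tuned: 1.2% / 3.4% / 2.9%, 2.4-fold (2.9/1.2).
- Logistic: 1.4% / 1.9% / 2.1%, 1.5-fold (2.1/1.4).

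Of 2,000 patients, 800 would be called low-risk. For the forest that means about 3 apparent misses (800 × 0.004) against about 29 true ones (800 × 0.036).

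**5. Other bootstrap variants.** The plain .632 estimate is 0.368 × apparent + 0.632 × out-of-bag. For the setting B forest it is 0.368 × 1.000 + 0.632 × 0.799 = 0.873, above logistic regression at 0.368 × 0.889 + 0.632 × 0.849 = 0.864, so the ranking is still wrong.

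The .632+ weight on the out-of-bag error is w = 0.632/(1 − 0.368R). Here R = (out-of-bag error − apparent error)/(0.5 − apparent error), and error is 1 − AUC. For the forest R = 0.201/0.5 = 0.402, w = 0.742, and AUC = 1 − 0.742 × 0.201 = 0.851. For logistic regression R = 0.040/0.389 = 0.103, w = 0.657, and AUC = 1 − (0.343 × 0.111 + 0.657 × 0.151) = 0.863. The order is now right, but the forest is still 0.851 − 0.812 = 0.039 too high.

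**The case against.** The strongest reply is that the article does not say what the concern needs. It names bootstrapping, not the optimism-corrected bootstrap. Out-of-bag validation is also bootstrapping, and it performs well above. The variant, the number of resamples and the nesting of tuning are details that a condensed article commonly leaves to the analysis plan. All of this stands, and it makes the point conditional.

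A reader might infer three stronger things that the documents do not support.

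- **That the ordinary bootstrap is planned.** The wording permits it but does not fix it.
- **That the wrong model will probably be chosen.** No selection measure is stated. Cross-validated deviance is already to be computed for the tuned models and could serve; in setting A, ten-fold cross-validated AUC ordered the models correctly (LASSO 0.859, boosting 0.841, forests 0.835 and 0.824).
- **That tuning inside bootstrap samples will go wrong.** The article does not say that tuning is repeated within resamples.

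It can also be said that an additive truth favours regression. That bears on which model is truly best, but not on the failed correction: in setting D, where trees truly outperform regression, the forests are still overstated by 0.14 to 0.19 and wrongly placed above boosting. Finally, random forests are listed with an and/or and may not be fitted; boosting alone is affected less.

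What survives is that the article gives one validation method for all model families, and that a common reading of it fails for some of them.

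**Conclusion.** The point holds conditionally. If the stated bootstrap is carried out as the optimism correction, AUC is overstated by about 0.08 to 0.3 for forests, depending on depth and setting, by about 0.03 to 0.09 for boosting, and by about 0.02 or less for regression. A tree model could be called best when it is not. The primary miss proportion could look too low, several-fold for a forest and less for boosting. If out-of-bag validation is meant, the problem largely disappears.

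The sizes rest on simulated predictors, chosen forms of truth, few data sets and resamples and, for the miss proportion, an assumed 40% cut. The direction and the contrast between families recurred in all five settings. This should be fixed, provided that an analysis plan not shown here does not already name a suitable variant.

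**What to change.** Replace the validation sentence with wording such as: *All model families are compared, and the proportion of high-risk patients among those classified low-risk is reported, on patients held out from model fitting, using repeated nested cross-validation or the out-of-bag bootstrap. Imputation, tuning and choice of cut-off are repeated within each training part.*

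The .632+ bootstrap is an acceptable alternative. It keeps some weight on apparent performance, though, so out-of-bag results should be shown beside it. The plain .632 should not be used for tree models.

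If tuning is repeated inside bootstrap samples, all copies of a patient must stay in the same fold. In setting A, cross-validated deviance for forest leaf sizes 1, 3, 10 and 30 was 1.03, 1.03, 1.04 and 1.08 on the original data. Inside a bootstrap sample it was 0.60, 0.72, 0.89 and 1.00, which strongly favours the smallest leaf. Nested cross-validation avoids this.

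The optimism bootstrap may stay as a supplement for the regression models.

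The cost is computing time and less favourable reported AUCs for the tree-based models. Data collection does not change.

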### Sample size

Sample size considerations were based on the three criteria of Riley et al. [27]:

i)small overfitting, defined by an expected shrinkage of predictor effects by 10% or less,ii)small absolute difference of 0.05 in the model’s apparent and adjusted Nagelkerke’s R-squared value, and.iii)precise estimation (within +/-5% points) of the average outcome risk in the population.

Assuming an event rate of 68%, an AUC of 0.85 [9] and considering 80 evaluated parameters (counting categorical variables as one parameter per degree of freedom), 1857 patients are needed in total. To be cautious and to compensate for missing data, 2,000 individuals will be included.

Calculations were performed by using the R language and environment for statistical computing (R Core Team, Vienna, Austria) version 4.2.3 with the pmsampsize package version 1.1.3.

### Patient and public involvement

None.

### Prehospital troponin analysis

Troponin I is being analysed during EMS missions using Siemens Healthineers Atellica VTLi patient side immunoassay analyser. Atellica VTLi is a point of care (POC) high-sensitivity troponin I assay with a level of detection (LoD) of 1.2 ng/L in plasma and 1.5 ng/L in whole blood, the limit of quantification based on a 20% coefficient of variation of 2.1 ng/L for plasma and 3.7 ng/L for whole blood. The sex-specific 99th percentile URLs were reported to be 27 ng/L for male patients and 18 ng/L for female patients [24–26]. Troponin is being analysed using either venous lithium heparinised whole blood or capillary whole blood depending on the study site and/or patient/personnel preferences.

The Atellica VTLi instruments are tested once each month by study representatives according to the manufacturer’s instructions.

Fifteen instruments are used for troponin I analyses. The instruments are stored at the EMS station in docking stations for battery charging. When EMS personnel are starting their shifts, an instrument is placed in the ambulance along with necessary blood sampling equipment. When caring for a patient with chest pain, the instrument is brought to the patient, and troponin is analysed bedside after retrieving informed consent for study participation. The Atellica VTLi must be in a horizontal position and stationary during the analysis process. Therefore, the analysis must be completed before initiating patient transport.

The analysis process takes about 8 min. The EMS personnel are instructed to initiate the troponin analyses as quickly as possible to minimise delay. Before the start of the study, the median time on the scene was approximately 25 min. This time frame allows the 8-minute analysis to be executed with minimal delay if initiated quickly after scene arrival. The EMS personnel are carefully instructed not to allow the results of the troponin analysis to affect clinical care. Most importantly, they should not recommend non-conveyance based on the troponin value achieved. Patients should, in all cases, be cared for only in line with organisational guidelines.

The EMS personnel are trained by Siemens Healthineers and/or study representatives on how to operate the Atellica VTLi. Study representatives are also available through the data collection period for further guidance and support.

Atellica VTLi cartridges for troponin I analyses require cold storage (+ 2-+8 °C). Cartridges can only be stored at room temperature for 24 h. Cold storage is not standard equipment in the ambulances of the current study sites. The need for cold storage is being handled in different ways for different study sites. Cartridges at densely populated sites with many EMS missions per shift are being kept at room temperature during the shift. If not used during the shift, the cartridges are jettisoned. For study sites with fewer EMS missions per shift, mini refrigerators, made for insulin travel storage, are installed in ambulances. These are powered by 5 V USB-A ports, 3.4 A, 10 W. Each mini refrigerator can store two cartridges.

### Ethics and dissemination

The study has been approved by the Swedish ethical review authority (Dnr 2022-01066-01 and 2022-06846-02). The study is observational, and there is no patient intervention other than retrieving blood samples. Patients are informed about the study both orally and in writing. Consent to participate in the study is confirmed in writing. The results of the study will be published in a peer-reviewed journal and will be presented at national and/or international conferences.

Data is being stored under pseudonyms making patient identification impossible without access to the hospital or EMS journal systems. Data is being stored using the data security and protection solutions of the regions included to minimise the risk for external data access.

### Present status and discussion

By December 2023, 380 EMS missions have been included. This is lower than expected. Inclusion has been hampered by malfunctioning of two of the instruments. One of them was due to reckless handling, and the other was due to the presentation of repeated error messages. Patient inclusion varies substantially between different study sites and between different EMS personnel. This variability indicates that the main reason for not including patients is a lack of compliance by EMS personnel, i.e., not recruiting eligible patients for inclusion. However, the inclusion rate has successively increased over time.

In approximately 15% of analyses with the Atellica VTLi, there is an error message, or the instrument is not able to provide a result. Early in the data collection period, unsuccessful troponin analyses were more common, which can probably be explained by instrument unfamiliarity and lack of training. In general, the Atellica VTLi is considered easy to use and functions well in the EMS setting. However, it should be taken into account that it is not always possible to obtain a troponin analysis result.

The process of obtaining informed consent in the EMS setting has previously been described as challenging [27, 28]. So far, the process of obtaining informed consent has not been an issue. The EMS personnel involved describe the process as easy, and few patients refuse to participate. The main challenge is instead to motivate EMS personnel to include eligible patients.

Situations concerning patients with a highly elevated troponin levels have been identified by the EMS personnel as difficult to handle. Personnel have been instructed to care for all patients in line with current guidelines. However, the EMS personnel describe a moral obligation to act upon elevated troponin value, by for example increasing pace of care or informing the receiving care unit regarding the elevated troponin levels.

As EMS personnel are not being blinded to the troponin value, the research team is fearful that EMS personnel may act on the results of the troponin analysis, by referring the patient to non-conveyance in the case of low troponin levels. They would thereby be deviating from current guidelines and potentially putting patients at risk by delaying care despite time-sensitive conditions.

A major challenge in the EMS setting is the need of keeping the Atellica VTLi cartridges cooled, despite the robustness and reliability of the mini refrigerators used. Substantial numbers of cartridges are jettisoned on a regular basis, resulting in increasing costs.

### Interim safety analysis

An interim analysis was conducted after the inclusion of the first 100 patients to ensure patient safety during the initial phase of the study. The primary objective of this interim analysis was to verify that no patients were non-conveyed based solely on troponin readings. This analysis served as an a priori safety check to confirm that EMS decisions regarding patient transport were based on a comprehensive clinical assessment rather than troponin results alone. Upon arrival at the scene, the EMS followed a standardised clinical guideline that includes a thorough evaluation of the patient’s clinical presentation, medical history, vital signs and ECG findings.

During the interim analysis, detailed data from 141 patients was reviewed to assess the EMS’ decision-making process. Each case was evaluated to determine the rationale behind the conveyance decision. Specifically, the analysis focused on identifying instances in which the troponin reading could have disproportionately influenced the decision not to transport a patient. Patient outcomes were tracked to identify any adverse events according to the definition or need for subsequent medical attention after a non-conveyance decision. This step ensured that patients who were not transported did not experience adverse outcomes that could have been prevented or mitigated by hospital transport.

Among the 141 patients, a total of 21 patients (14.9%) were not conveyed after assessment by the EMS. The rate of non-conveyance is thus similar to, and even lower than, that of the patient population with chest pain assessed within the EMS organisations (approximately 20% non-conveyance rate). In accordance with the study outcome, we encourage EMS personnel to obtain a full history of the patient care event, including physician diagnosis at hospital discharge, which may explain the increased conveyance rate. Moreover, since the troponin analysis results are not being blinded, elevated troponin levels could result in transporting patients to the ED also in the case of patients who would normally be non-conveyed.

Of the patients who were non-conveyed and referred to lower levels of care, seven patients (33%) sought emergency care and were admitted to the ED within 72 h. An evaluation of patient outcomes revealed that none of the non-conveyed patients fell into the high-risk category. All but one were classified as low-risk. This single patient in the intermediate-risk category was classified based on the final diagnosis, in accordance with the study definitions previously described by Wibring et al. [6].

